Criteria of dropout include the following: (1) consent withdrawn by the participants themselves (at least one dose of study drug has been administered); (2) loss to follow‐up; (3) ordered to exit by the investigators or attending physicians (poor compliance, occurrence of severe complications, or occurrence of severe adverse events); (4) prophylactic use of any prohibited drugs (anticholinergics or any medications other than the study drugs) from study recruitment to postoperative day 2; or (5) blindness unmasked. For dropout cases, detailed reasons will be recorded in the case report forms (CRFs). The primary therapeutic effects recorded the last time will be regarded as the final results. These cases will be included in the intention-to-treat analysis but excluded from the per protocol analysis.

Criteria of rejection include the following: (1) consent withdrawn by the participants themselves (study drug is not administered); (2) no study record; or (3) surgery delayed or canceled, unable to assess the occurrence of PPCs. For rejected cases, detailed reasons will be recorded in the CRFs. These cases will be excluded from analysis of therapeutic effects.

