### Anesthesia and perioperative management

Intraoperative monitoring include electrocardiogram, pulse oxygen saturation, noninvasive blood pressure, airway pressure, end-tidal carbon dioxide concentration, nasopharyngeal temperature, urine output, and bispectral index (BIS) value. Intra-arterial pressure (and derivative parameters such as stroke volume variation by FloTrac system) and central venous pressure are monitored when considered necessary.

Anesthetic premedication is not administered. Prophylactic antibiotics (the first or second generation cephalosporin, with or without metronidazole, or cephamycins) are administered 30 minutes to 1 hour before surgical incision. The duration of prophylactic antibiotic treatment is less than 48 hours. The choice of antibiotics and the duration of prophylactic antibiotic therapy are decided according to the *Guiding Principles of Clinical Use of Antibiotics* (published by Chinese National Health and Family Planning Commission in 2015) http://www.nhfpc.gov.cn/zwgkzt/wsbysj/200804/18544.shtml. Therapeutic antibiotic agents are only indicated in patients who are diagnosed with infection.

General anesthesia with endotracheal intubation is performed for all patients. Anesthesia is induced with intravenous propofol or etomidate, sufentanil, and rocuronium, or cisatracurium, and maintained with intravenous propofol, remifentanil and/or sufentanil, and rocuronium or cisatracurium, with or without inhalational sevoflurane and/or nitrous oxide. Neuraxial block is performed depending on the decision of attending anesthesiologists. BIS value is maintained between 40 and 60. Mechanical ventilation is established with a tidal volume from 6 to 8 ml/kg, a positive end-expiratory pressure from 0 to 5 cm H2O, a frequency from 12 to 16 breaths per minute, and 50% oxygen (mixed with nitrous oxide or air). Higher oxygen concentration is administered during one-lung ventilation. Fluid management is performed according to routine practice. Packed red blood cells are transfused to maintain a hemoglobin level above 7 g/dl. Anticholinergics are prohibited unless being used for the treatment of bradycardia, in which case atropine is administered.

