At the end of surgery, patients are transferred to the postoperative care unit (PACU) after extubation and monitored for at least 30 minutes before being sent back to the general wards. For patients who are transferred to the intensive care unit (ICU) with endotracheal intubation, propofol and/or dexmedetomidine sedation are provided in addition to opioid analgesia; mechanical ventilation is performed with bilevel ventilation mode (established with a low level at 3 to 5 cm H_2_O, a high level between 13 and 16 cm H_2_O, and a trigger flow at 2 to 3 l/min; PB 840 ventilator, Puritan-Bennett Corp., Mervue, Ireland). Patients are extubated as soon as they meet the criteria of extubation (regain consciousness and airway protective reflex, normal circulatory status and temperature, no residual neuromuscular blockade). For patients requiring mechanical ventilation of more than 24 hours, a ventilator weaning protocol is executed in order to extubate patients as soon as possible (Additional file 2). For patients with acute respiratory failure, noninvasive positive pressure ventilation is used to promote early extubation or to avoid reintubation. For all patients after extubation, low-flow supplemental oxygen is routinely provided during the day of surgery.

During the postoperative period, patient-controlled analgesia (either intravenous or epidural) is provided for up to 3 days after surgery. The target is to maintain a Numeric Pain Rating Scale (NPRS, an 11-point scale where 0 = no pain and 10 = the worst pain) pain score of 3 or less. Nonsteroidal anti-inflammatory drugs are administered when considered necessary and without contraindications. Other treatments including chest physiotherapy, early mobilization, removal of nasogastric tube, parenteral or enteral nutrition, and intravenous respiratory medications (such as expectorants, theoclears and glucocorticoids) are administered according to routine practice.

During the study period, inhalations of any respiratory medications for prophylactic purpose other than the study drugs are prohibited. However, for patients who develop PPCs, inhalation of respiratory medications is allowed. For those who develop harmful effects or clinical deterioration, the dose of study drugs can be decreased or the study drug administration can be discontinued on request of participants, attending surgeons or investigators. These situations will be recorded in the CRFs.

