### Data analysis

#### General principles

All statistical analyses will be performed with SPSS 14.0 software package (SPSS, Chicago, IL, USA) and SAS 9.2 software (SAS Institute, Cary, NC, USA) by statisticians in the Department of Biostatistics of Peking University First Hospital. Since the safety of intervention has been confirmed by our previous pilot study, interim analysis is not planned. Analyses will be performed on an intention-to-treat basis, that all subjects will be analyzed in the group which they were assigned to. For the primary outcome (the incidence of PPCs within 30 days after surgery), per protocol analysis will also be performed.

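### Dropout criterion 4 defines prohibited drugs so widely that, as worded, it conflicts with the protocol's own antibiotic prophylaxis and leaves the per-protocol set badly fixed

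*Protocol article*

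**What the plan says.** Four statements in the protocol article bear on this point.

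- **Dropout rule (Participants).** The fourth criterion for dropout is "prophylactic use of any prohibited drugs (anticholinergics or any medications other than the study drugs) from study recruitment to postoperative day 2". Of dropouts in general the section says: "These cases will be included in the intention-to-treat analysis but excluded from the per protocol analysis".
- **Antibiotics (Anesthesia and perioperative management).** Prophylactic antibiotics "are administered 30 minutes to 1 hour before surgical incision", and "The duration of prophylactic antibiotic treatment is less than 48 hours". The choice of drug and the duration follow a national guideline. No group of patients is exempted.
- **Drug prohibitions (same section).** There are two. The first is "Anticholinergics are prohibited unless being used for the treatment of bradycardia, in which case atropine is administered". The second is that "inhalations of any respiratory medications for prophylactic purpose other than the study drugs are prohibited".
- **Role of the per-protocol analysis (General principles).** Analyses follow intention-to-treat. Then: "For the primary outcome (the incidence of PPCs within 30 days after surgery), per protocol analysis will also be performed".

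**The concern.** Criterion 4 turns on the term prohibited drugs and then defines that term itself, in brackets, as anticholinergics or anything that is not study drug. A prophylactic antibiotic is a prophylactic medication that is not study drug. The protocol directs that it be given, and it is given within the period that the criterion covers. A patient treated exactly as the management section describes therefore meets a dropout criterion.

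At stake is the membership of the per-protocol set. If the text cannot be applied as it stands, someone has to decide later what it meant, and the article does not say who or when. If that happens after outcomes are known by arm, the set is no longer pre-specified, and agreement or disagreement with the intention-to-treat result tells the reader less.

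**Working it through.** **Step 1: does the antibiotic fall inside the window?** The criterion runs from recruitment to postoperative day 2. Patients are recruited the day before surgery, or on Friday for Monday surgery (Patient recruitment and baseline data collection). The antibiotic starts 30 minutes to 1 hour before incision. It is therefore given after recruitment and before postoperative day 2, whatever its duration.

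**Step 2: set the two definitions side by side.**

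| | Criterion 4 (Participants) | Prohibitions (Anesthesia and perioperative management) |
|---|---|---|
| Anticholinergics | Included, if prophylactic | Prohibited, except to treat bradycardia |
| Other drugs | Any medication that is not study drug, if prophylactic | Only inhaled respiratory medications, if prophylactic |
| Prophylactic antibiotic | Caught as worded | Directed, not prohibited |

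The two columns agree on anticholinergics: atropine for bradycardia is treatment, so the word prophylactic already leaves it out of criterion 4. They disagree on all other drugs. The criterion is limited neither to inhaled drugs nor to respiratory drugs.

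**Step 3: size.** Let f be the share of patients given the prophylactic antibiotic. The article gives no value for f, but it describes the antibiotic without exempting anyone. Under the literal wording, the per-protocol number per group before any other exclusion is 432 × (1 − f). At f = 1 this is 432 × 0 = 0. Under the narrower meaning, the antibiotic excludes nobody and 432 per group remain.

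Power between these two ends can be shown with the design rates, 42.1% and 32.1% (reading the 10% reduction as absolute), one-sided 0.025, n per group, mean rate 0.371:

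power = Φ{[0.10√n − 1.96√(2 × 0.371 × 0.629)] / √(0.421 × 0.579 + 0.321 × 0.679)}

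The values of f below are assumptions, chosen only to span the range.

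| f | n per group | Per-protocol power |
|---|---|---|
| 0 | 432 | 86% |
| 0.5 | 216 | 58% |
| 0.8 | 86 | 27% |
| 1 | 0 | undefined |

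**Step 4: is the design figure touched?** The article states 360 per group. The same rates, with 80% power and no continuity correction, give 366 (pooled variance) or 363 (unpooled), and 360 per group has 79.4% power. The stated figure therefore reproduces closely. No input to it comes from the wording of criterion 4.

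**The case against.** The best reply is that the criterion governs only prohibited drugs, and the rest of the article shows what those are. The bracket names anticholinergics and then uses the phrase other than the study drugs, which also closes the ban on prophylactic inhalation. Most likely the words limiting it to inhaled respiratory drugs were lost. An antibiotic that the protocol directs cannot sensibly be called prohibited, and a reading that empties the set is evidence against itself.

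Most of this stands. The narrower meaning is probably the intended one, and it would be wrong to say that the per-protocol set will in fact exclude compliant patients. But the criterion does not refer to the prohibitions elsewhere. It supplies its own definition, and that definition is wider. A rule that works only when its words are overridden is wrongly stated, which is different from detail left to an analysis plan.

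A reader might go further in three ways that the documents do not support.

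- **Intravenous drugs.** The management section says that "intravenous respiratory medications (such as expectorants, theoclears and glucocorticoids) are administered according to routine practice". It does not call this use prophylactic, and it permits it, so these patients cannot be counted as dropouts under a respiratory-drug reading.
- **Different windows.** Criterion 4 stops at postoperative day 2, while the inhalation ban applies during the study period. Study-drug dosing also ends on postoperative day 2, so limiting a per-protocol exclusion to the dosing period is a legitimate choice. The article does not define the study period as running to day 30.
- **Selection of lower-risk patients.** No statement in the article supports the idea that the set would be tilted towards lower risk, and none gives the share of patients who receive other respiratory drugs.

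**Conclusion.** The point holds as a conflict of wording with a real consequence for one analysis set. Applied literally, criterion 4 excludes every patient given the prophylactic antibiotic: all 432 per group if everyone receives it. Under the narrower meaning it excludes none of them. The first result assumes that antibiotic prophylaxis is universal, which the article implies but does not count. The second assumes that the bracket was meant to repeat the prohibitions in the management section.

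The effect stops at the additional per-protocol analysis of the primary outcome. A reader might infer that the main result is also at risk, because the last recorded effects of a dropout count as final. The documents do not support that. Dropouts stay in the intention-to-treat analysis, and the section on patient follow-up says that follow-up is completed for patients who deviate from the intervention protocol. The sample size calculation is unaffected. The correction should be made because it costs almost nothing, but the point does not threaten the trial's main conclusion.

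**What to change.** Reconcile the dropout criteria in Participants with the antibiotic and drug-prohibition statements in Anesthesia and perioperative management. In criterion 4, replace the bracketed definition with a reference to one definition of prohibited drugs, used throughout the protocol, so that the per-protocol set excludes only use of what the protocol itself prohibits. Which drugs belong in that definition is for the investigators to settle. Record the agreed definition, with its date, before unblinding.

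The cost is one sentence in the dropout criteria. The change concerns who enters the per-protocol set and need not alter patient care, the intention-to-treat analysis or the sample size.

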### Patient follow-up and outcome assessment

Patients will be followed up twice daily until postoperative day 2, once daily from postoperative days 3 to 6, and then weekly until 30 days after surgery. Intraoperative data including type and duration of anesthesia, uses and doses of anesthetics, analgesics and other drugs, parameters of mechanical ventilation, fluid balance and transfusion of blood products, as well as type and duration of surgery will be collected. The final cumulative ARISCAT risk score will be calculated just after the surgery. Postoperative data including NRS pain scores, analgesic consumption, respiratory management, return of gastrointestinal function, start of nutrition, occurrence of complications and related treatment, admission to the ICU, duration of hospital stay, and any events that lead to return or readmission to hospital after hospital discharge will be recorded. Any adverse events or complications that occur during the study period will be promptly treated according to routine practice. For patients who deviate from the intervention protocol, deviations will be corrected when possible and follow-up will be completed. For patients who withdraw consent, the last follow-up results will be regarded as the final results.

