#### Outcome analysis

Primary outcome (the incidence of PPCs within 30 days after surgery) will be compared with χ2 test. The difference between groups and the 95% confidence interval of the difference will be calculated.

For secondary outcomes, continuous variables with normal distribution will be analyzed using an unpaired *t* test; continuous variables with abnormal distribution or ranked data will be analyzed using Mann-Whitney *U* test; categorical variables will be analyzed using the chi-squared test, continuity correction chi-squared test or Fisher exact test; time-to-event results will be analyzed using the Kaplan-Meier estimator, and the differences between groups will be tested by the log-rank test. Subgroup analyses will be performed according to the type of the surgery (upper abdominal or thoracic).

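### Dropouts' last recorded result is taken as their 30-day result, so a patient who leaves event-free is counted as PPC-free in the primary comparison

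*Protocol article*

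**What the plan says.** The Participants section of the protocol article lists five kinds of dropout: consent withdrawn after at least one dose, loss to follow-up, exit ordered by investigators or physicians, prophylactic use of a prohibited drug, and unmasking. For all of them it says "The primary therapeutic effects recorded the last time will be regarded as the final results", and then "These cases will be included in the intention-to-treat analysis but excluded from the per protocol analysis".

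The section Patient follow-up and outcome assessment repeats the rule for one class: "For patients who withdraw consent, the last follow-up results will be regarded as the final results". The sentence before it treats another group differently: "For patients who deviate from the intervention protocol, deviations will be corrected when possible and follow-up will be completed".

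The primary outcome is the incidence of PPCs of Clavien-Dindo grade II or above within 30 days (Primary outcome). It is compared by a chi-squared test, with a 95% confidence interval for the difference (Outcome analysis). The only other stated analysis of this outcome is per protocol (General principles). The sample size section allows for a dropout rate of about 20% and does not break it down by reason.

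**The concern.** The endpoint is cumulative: a patient is a non-event only after being observed without a PPC up to day 30. Carrying the last result forward turns no event yet into no event at all for anyone who leaves event-free. The intention-to-treat label then covers a single imputation of the favourable outcome.

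If exits are equally frequent and equally early in both arms, the observed rates and their difference shrink and power falls. If they differ, the arm that loses more patients gains an apparently lower PPC rate. Some exit reasons could depend on treatment or outcome. One class is "ordered to exit by the investigators or attending physicians (poor compliance, occurrence of severe complications, or occurrence of severe adverse events", and the adverse events the protocol lists as possible include dry mouth, palpitation and delirium. More exits on penehyclidine would favour the drug falsely; more exits on placebo would hide a benefit. The per protocol analysis does not help, because it removes the same patients.

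**Working it through.** **Inputs.** From the sample size section: placebo rate 42.1%, reduction 10 points (so 32.1%), one-sided level 0.025, 80% power, 360 per group, about 20% dropout, 432 enrolled per group. Assumptions, because the document gives no figure: *f*, the share of dropouts' PPCs that go unrecorded; the dropout share *d* in each arm; and that dropouts have the same underlying PPC risk as other patients in their arm.

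**Plan's own figure.** The unpooled formula is n = (1.960 + 0.842)² × (0.421 × 0.579 + 0.321 × 0.679) / 0.10² = 363 per group. The pooled-variance version gives 366. Both are close to the stated 360. A relative reduction of 10% would need 2,125 per group, so the 10% is absolute. The enrolled 432 is 360 × 1.2.

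**Equal dropout.** Under the rule, the observed rate is p × (1 − d × f). Power is for the one-sided pooled z-test (equivalent to the chi-squared test without continuity correction) at 432 per arm, with d = 0.20 in both arms:

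| f | Placebo | Penehyclidine | Difference | Power |
|---|---|---|---|---|
| 0 | 42.1% | 32.1% | 10.0 points | 86.2% |
| 0.5 | 0.421 × 0.9 = 37.9% | 0.321 × 0.9 = 28.9% | 9.0 points | 80.2% |
| 1 | 0.421 × 0.8 = 33.7% | 0.321 × 0.8 = 25.7% | 8.0 points | 73.1% |

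Power drops below the planned 80% once slightly more than half of the dropouts' PPCs are missed, which is about 10% of all PPCs.

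**Unequal dropout, no true effect.** With 42.1% in both arms, the spurious difference is 0.421 × f × (d on penehyclidine − d on placebo). The chance of one-sided significance in favour of penehyclidine, nominally 2.5%, is:

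| Exits, penehyclidine vs placebo | f = 0.5: bias, error | f = 1: bias, error |
|---|---|---|
| 6% vs 4% | 0.4 points, 3.3% | 0.8 points, 4.4% |
| 22% vs 18% | 0.8 points, 4.4% | 1.7 points, 7.5% |
| 24% vs 16% | 1.7 points, 7.4% | 3.4 points, 18.1% |

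For example, 0.421 × 1 × (0.24 − 0.16) = 0.034.

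**The two sections side by side.** Take a patient unmasked on day 1 who develops a PPC on day 5. If the status at exit is final, as the Participants section can be read, there is no event. If follow-up is completed, as the follow-up section can be read, there is an event. The text does not settle which applies.

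**The case against.** The strongest reply is that the two sections are compatible. The follow-up section says that for patients who depart from the intervention protocol "deviations will be corrected when possible and follow-up will be completed", and it names only consent withdrawal for the last-result rule. On that reading, a patient who is unmasked, given a prohibited drug or poorly compliant is observed to day 30, the last record is the day-30 record, and the rule changes nothing. This reading is fair, and it means a reader should not infer a flat contradiction. But the Participants section puts these patients under the same rule as those truly lost, so the ambiguity remains.

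A second reply also stands: the 20% is not 20% missing outcomes. The protocol's dropout category mixes deviations with loss of data. Contacts are twice daily to day 2, daily on days 3 to 6 and weekly afterwards, so any PPC recorded before exit is kept, and an exit ordered for a severe complication may itself follow a recorded PPC. The rows with f = 1 are upper ends, and the arm imbalances are assumed, not taken from the document.

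A reader might also infer that a patient who withdraws after one dose but before surgery is expressly counted as a success, since the dropout class needs only "consent withdrawn by the participants themselves (at least one dose of study drug has been administered" and dosing starts the evening before surgery. The documents do not say so. Such a patient has no postoperative result to carry forward, and the case is undefined.

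Finally, time to onset of PPCs is a secondary outcome, and "time-to-event results will be analyzed using the Kaplan-Meier estimator", a method that can censor at last contact. That is useful supporting evidence, but it does not change the primary chi-squared comparison. An analysis plan that is not shown may add sensitivity analyses, and their absence is not criticised here. The point is the rule that the protocol itself fixes.

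**Conclusion.** The point holds in this form. The protocol fixes a carry-forward rule that suits a cumulative 30-day yes/no endpoint badly, and applies it to the primary analysis. Its certain reach is consent withdrawal, loss to follow-up and ordered exits whose follow-up stops. For unmasking and prohibited drugs, its reach depends on how the two sections are reconciled.

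The effect runs from nothing to a loss of 2 of the 10 points and 13 percentage points of power (86.2% to 73.1%) when dropout is 20% in both arms. For type I error, a small true loss (6% vs 4%) gives 3.3% to 4.4%, and the larger assumed imbalances give 4.4% to 18.1%. All of this rests on assumed exit timing and arm imbalance. None of it is a forecast, and the upper figures should not be read as the expected bias.

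**What to change.** Reconcile the two sections. State that stopping study drug, unmasking or use of a prohibited drug does not end outcome collection, and that PPC status is collected to day 30 for every randomised patient except those who refuse further contact. Say explicitly how a patient who withdraws before surgery is handled.

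For 30-day status that is truly unobserved, treat it as missing in the primary analysis, for example by multiple imputation by arm and type of surgery using the data up to exit. Add a tipping-point sensitivity analysis. Keep the last-result rule at most as a further sensitivity analysis. A Kaplan-Meier 30-day risk difference with censoring at last contact is an alternative only if censoring is uninformative, which is doubtful for exits ordered because of complications.

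The cost is wording, some extra analysis work and slightly wider intervals. The contacts to day 30 are already scheduled. The change should be made before database lock and unblinding.
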